### Randomisation and blinding

An independent researcher who is not involved in the trial performs the randomisation (centrally from Amsterdam) at an individual level, stratified by country after eligibility and baseline measurement. A computerised random number generator (Random Allocation Software) will be applied with an allocation ratio of 1:1. Block randomisation will be used with variable block sizes that vary between eight and fourteen allocations per block.

The assessors for eligibility will be blinded to group allocation. During treatment, blinding of participants and clinicians are naturally impossible. Researchers and statisticians involved in the analyses will be blinded to group allocations. The groups will be numbered in the dataset without revealing which treatment was given. The questionnaires administered solely to the B-CBT group will be analysed in a separate dataset.

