### Outcome measurements

Baseline measures will be administered after consent has been granted prior to randomisation. The participants will be followed up three-, six-, and twelve months after baseline measurement. In case of drop-out, a short questionnaire regarding reasons for drop-out will be administered. All questionnaires for the participants will be administered online. A secure web application for building and managing online surveys (RedCap) will be used for all questionnaire packages except the weekly monitoring for the B-CBT group, which will be administered from within the treatment programme. See Table 2 for an overview of measurements and time points. Data is stored by Odense Patient data Exploratory Network. Data is managed by a local data manger with training and prior experience in datamangement. The datamanager quality checks data continuously. Data is collected, transferred, and stored securely electronically and is approved by the Danish Data Protection Agency (J.nr.: 14/26634 Reg. nr.: 2008-58-0035).

**Table 2 Tab2:** Overview of measurements

Variable	Instrument	Items	Time (mins)	Screening Baseline	Weekly	3 months	6 months	12 months
Questions taken from participants								
Demographics		n/a	1	X				
Current treatment		n/a	2	X				
Diagnostic interview	M.I.N.I.	n/a	15	X				X
Depressive symptoms	QIDS-SR16	16	3	X	Item 12	X	X	X
	PHQ-9	9	2	X	X	X	X	X
Treatment preference		1	1	X				
Patient expectancy	CEQ	8	2	X				
Working alliance	WAI-SF	12	3			X		
Technology alliance	TAI-SR^a^	12	3			X		
Client satisfaction	CSQ-8	8	3			X		
Satisfaction with the online programme	SUS^a^	20	3			X		
Drop-out	Number of sessions completed - data extraction	n/a	0				X	
	Patients reason for drop-out. Questionnaire	3	2				X	
Questions taken from therapists								
Working alliance	WAI-SRT	12	3			X		
Satisfaction with the online programme	SUS^b^	20	3			X		

^a^Offered to condition receiving blended treatment only, ^b^Has to be completed once per therapist after completion of the first treatment

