#### Secondary outcomes

The Quick Inventory of Depressive Symptomatology Self-Report (QIDS-16-SR) [33] is used in addition to the PHQ-9 because it is a promising questionnaire for assessing depressive symptoms especially in specialised mental health care, whereas the PHQ-9 is developed for use in primary care. The QIDS-16-SR is a questionnaire that screens for depressive symptoms and assesses depression severity. It consists of 16 items each scored on a 0–3 point scale and includes symptom domains of MDD based on DSM-IV. The QIDS-16-SR has shown good psychometric properties [33, 34].

The Client Satisfaction Questionnaire (CSQ-8) [35] is used to measure the patients’ satisfaction with the treatments. The questionnaire consists of eight items measured on a four point scale with total scores ranging from 8–32 and has shown good psychometric properties [36]. Clinician satisfaction with the treatment will be assessed by the short form of the Client Satisfaction Questionnaire including only the three core questions of the csq-8.

To measure the patients’ expectancy and judgement of credibility of the treatments the Credibility and Expectancy Questionnaire (CEQ) [37] is used. The CEQ is a two part questionnaire measuring credibility and expectancy respectively. Both factors have been shown to be stable across different populations, with high internal consistency within each factor [37].

To indicate whether a difference is seen in the therapeutic alliance the short version of the Working Alliance Inventory (WAI-SR) is used. WAI-SR is a 12 item self-report questionnaire with responses on a five point Likert scale ranging from 1 (never) to 5 (always) [38, 39]. The questionnaire covers three dimensions of working alliance: (1) therapeutic goals, (2) tasks, and (3) bond and the sub scales have demonstrated good internal consistencies [40]. Both the patient and the ten items therapist version of the questionnaire will be administered. The alliance between the patient and the programme will be assessed with the WAI Online Therapy (TAI)(Labpsitec, 2014).

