## Sample size and statistical analyses

The primary outcome is analysed by regressing the three-month follow-up PHQ-9 data on the baseline PHQ-9 score and a treatment group indicator. We will use an ancova model for this purpose. Missing values are handled using a full-information maximum likelihood estimator. In case of dropout, we will use the last observed values in a supplementary intention-to-treat analysis. Missingness sensitivity will be assessed with a best-/worst-case comparison, where missing values are replaced with the minimum and maximum values observed at follow-up.

The primary hypothesis is that the blended care intervention will be no less effective than the TAU intervention in reducing depression symptoms. A sample size of 130 in two balanced groups will yield a power of at least 80% to detect standardised mean differences above 0.5 on a normally distributed variable. This equivalence interval is slightly narrower than other estimates of minimally clinically important differences [43].

In addition, we will compare the development of PHQ-9 in the two groups using the weekly measurements in a mixed effects model. We will model the individual trajectories as random slopes, and then let the treatment group predict the slopes. Significant slope differences between groups will indicate either faster or slower treatment effects in the blended care group. In case of non-normal data, we will use an appropriate measure of transformation or a generalised linear model. Variables with significant variations between groups at baseline are introduced as control variables.

Secondary outcomes will be analysed using t-tests or a rank sum test. Where appropriate, differences between baseline and follow-up scores are used as outcomes instead of only comparing the follow-up score.

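### QIDS-SR16 is to be compared without baseline adjustment although its baseline is collected and the primary analysis already uses ANCOVA: a free gain in precision

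*Protocol article*

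**What the plan says.** All the relevant analysis text is in the protocol article, under Sample size and statistical analyses. The primary analysis is baseline-adjusted: "The primary outcome is analysed by regressing the three-month follow-up PHQ-9 data on the baseline PHQ-9 score and a treatment group indicator", by ANCOVA. The other outcomes get a different treatment: "Secondary outcomes will be analysed using t-tests or a rank sum test". The next sentence adds: "Where appropriate, differences between baseline and follow-up scores are used as outcomes instead of only comparing the follow-up score". It does not say which scales or time points are meant.

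Under Secondary outcomes, "The Quick Inventory of Depressive Symptomatology Self-Report (QIDS-16-SR) [33] is used in addition to the PHQ-9", the stated reason being that it is promising in specialised mental health care. Under Outcome measurements, "The participants will be followed up three-, six-, and twelve months after baseline measurement". Table 2 marks QIDS-SR16 at baseline, 3, 6 and 12 months. The other named secondary scales lack one or the other: CSQ-8, WAI, TAI and SUS have no baseline, and CEQ is taken at baseline only.

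**The concern.** The trial measures depressive symptoms with two self-report scales on the same schedule of baseline and follow-ups. One is adjusted for its baseline at three months. The other, QIDS-SR16, is to be compared by a test that cannot carry a covariate, on either the raw follow-up score or the change score, and no reason is given for the difference.

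Baseline-adjusted ANCOVA estimates the slope on baseline from the data. A follow-up comparison fixes that slope at 0 and a change-score comparison fixes it at 1. Unless the true slope happens to equal the fixed value, information already collected is discarded and the confidence interval for the second depression scale is wider than it need be. Leaving open which of the two scores is used adds an avoidable ambiguity about which result will be reported.

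**Working it through.** **Inputs from the protocol.** Total sample 130, allocated "with an allocation ratio of 1:1", hence 130/2 = 65 per arm, with a standardised mean difference of 0.5.

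**Inputs assumed, because the protocol does not state them.** Two-sided alpha 0.05; baseline-to-follow-up correlation r of QIDS-SR16 from 0.3 to 0.7; ratio k of baseline SD to follow-up SD, first 1, then 0.7.

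**Step 1: the plan's own figure.** The protocol says "A sample size of 130 in two balanced groups will yield a power of at least 80" per cent "to detect standardised mean differences above 0.5 on a normally distributed variable". With 65 per arm and SD 1, the standard error is √(2/65) = 0.1754. Power is Φ(0.5/0.1754 − 1.96) = Φ(0.89) = 0.813 (0.808 with the t distribution). The figure reproduces. It refers to the primary outcome and takes no credit for baseline adjustment. The protocol gives no power figure for secondary outcomes.

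**Step 2: relative variances of the group difference.** With follow-up variance set to 1:

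- follow-up score only: 1
- change score: 1 + k² − 2kr, which is 2(1 − r) when k = 1
- ANCOVA: 1 − r²

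Subtracting, the follow-up score exceeds ANCOVA by r² and the change score exceeds it by (k − r)². Neither can be negative, so to first order ANCOVA is never the less precise choice, whatever r and k are.

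**Step 3: equal SDs (k = 1).**

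| r | Follow-up | Change | ANCOVA | Excess, follow-up | Excess, change |
|---|---|---|---|---|---|
| 0.3 | 1.00 | 1.40 | 0.91 | 1.00/0.91: 10% | 1.40/0.91: 54% |
| 0.5 | 1.00 | 1.00 | 0.75 | 1.00/0.75: 33% | 1.00/0.75: 33% |
| 0.7 | 1.00 | 0.60 | 0.51 | 1.00/0.51: 96% | 0.60/0.51: 18% |

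Interval width goes with the square root of variance. At r = 0.5, √1.333 = 1.15, so either planned comparison gives an interval about 15% wider than ANCOVA.

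**Step 4: smaller baseline SD (k = 0.7).** The change-score variance becomes 1 + 0.49 − 1.4r.

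- r = 0.3: 1.07 against 0.91, an excess of 18% instead of 54%
- r = 0.5: 0.79 against 0.75, an excess of 5% instead of 33%

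The follow-up excess depends only on r and does not change.

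**Step 5: the same loss in power and patients.** As an illustration, take a difference of 0.5 follow-up SDs on QIDS-SR16, 65 per arm and k = 1. Each cell gives follow-up / change / ANCOVA.

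| r | Power | Total N for 80% power |
|---|---|---|
| 0.3 | 0.813 / 0.673 / 0.848 | 126 / 176 / 116 |
| 0.5 | 0.813 / 0.813 / 0.908 | 126 / 126 / 96 |
| 0.7 | 0.813 / 0.957 / 0.979 | 126 / 76 / 66 |

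**Step 6: the choice of score.** Once baseline is a covariate, using the change score or the follow-up score as response gives the same treatment estimate, since subtracting baseline only shifts the baseline slope by 1. The model therefore removes that choice.

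**The case against.** The strongest reply is about scope and size. Only one named secondary scale is affected. Follow-up and change-score tests are valid in a randomised trial. The correlations are assumed, and entry criteria (major depressive disorder and a PHQ-9 of at least 5) make a restricted baseline SD plausible, which shrinks the change-score loss as Step 4 shows. In favourable corners with equal SDs the loss is slight: 1.00 against 0.96 for the follow-up score at r = 0.2, and 0.40 against 0.36 for the change score at r = 0.8. All of this stands and limits the weight of the point.

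It can also be said that the sentence has a natural reading, with change scores where a baseline exists, follow-up scores where none does, and the rank sum test for skewed data, and that an article may leave such assignments to an analysis plan that is not shown. That is fair as to missing detail. It does not remove the point, because the article does name the methods, and under every reading of them QIDS-SR16 is left unadjusted.

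A reader might infer inflated type I error. If the score were chosen after the fact by the smaller p-value, simulation of 100,000 trials per correlation (equal SDs) gives a two-sided error of about 0.088 to 0.093 for r from 0.3 to 0.7, instead of 0.05. Nothing in the protocol says that the choice would be made in that way, so this describes a risk of loose wording and not the plan.

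A reader might also say that a rank sum test yields no usable estimate. That is too strong: a location-shift estimate with a confidence interval can accompany it on the score scale.

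**Conclusion.** The point holds as a free improvement. For QIDS-SR16 the protocol names a less precise analysis than the one it already uses for PHQ-9, and leaves open which score is compared. The direction needs no assumption about r or the SD ratio, apart from the special cases where the loss is zero. The size does: over the assumed r of 0.3 to 0.7, the excess variance runs from 10% to 96% for the follow-up score, and from 18% to 54% for the change score with equal SDs. The change-score loss is smaller at r = 0.3 to 0.5 if the baseline SD is the smaller one.

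Two wider readings are not supported. PHQ-9 at 6 and 12 months might seem to be covered by the same sentence, but those time points are not listed under Secondary outcomes and the protocol does not say how they are analysed. QIDS-SR16 might also seem to carry part of the non-inferiority claim, but the protocol gives it no margin and no such role.

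**What to change.** Analyse QIDS-SR16 at 3, 6 and 12 months by regressing the follow-up score on its own baseline and treatment group. Report the adjusted difference with a 95% confidence interval, using a robust or bootstrap interval if residuals are skewed. If PHQ-9 at 6 and 12 months is to be analysed as a secondary outcome, say so and use the same model. Keep the t-test or rank sum test for scales without a baseline, such as CSQ-8 and WAI.

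The cost is a change of wording in the analysis text. The baseline is already collected and the model is already specified for the primary outcome, so no extra data or patients are needed.

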## Discussion

The present study aims to investigate the clinical effectiveness of CBT delivered in a format in which face-to-face consultations are alternated with online self-help modules, since this could hold promise to combine advantages of Internet based guided self-help and traditional CBT while preserving the clinical effectiveness and broad applicability of traditional CBT.

It is a strength of the present study, that the treatment in the two conditions have similar therapeutic content given that both treatments are captured in one coherent treatment manual detailing each intervention. Consequently, the study will reveal a very direct comparison with a minimum of the variance explained by differences in therapeutic methods.

The study is limited, however, by the fact that even though it is situated in specialised mental health care, patients are recruited from a clinic offering self-referral. Consequently, the results may be hard to generalise with regards to future implementation.

The present study will contribute to the knowledge in the field by comparing, in a direct and concise manner, B-CBT to the well known and well investigated traditional face-to-face CBT, which in many settings is considered the golden standard of psychotherapeutic treatment of depression.
